#### Fall-incidents

Patients will be asked to report all fall incidents weekly in a fall diary for a period of three months after discharge. A fall is defined as "an unintentional change in position resulting in coming to rest at a lower level or on the ground" [30].

#### Bio-electrical impedance spectroscopy

Bio-electrical impedance spectroscopy (BIS) will be applied to calculate (changes in) body composition. Measurements will be performed at the non-dominant side of the patient, using a Hydra ECF/ICF Bio Impedance Spectrum Analyzer, model 4200 (Xitron Technologies, San Diego, CA, USA). Shoes, socks and jewellery will be removed and patients will be in supine position. Two current electrodes (tetra-polar electrodes (3 M red Dot AG/AgCl)) will be placed at the dorsal surfaces of the hand and foot on the distal position of the second metacarpal and metatarsal, respectively. Two detector electrodes will be placed at the posterior wrist between the styloid processes of the radius and ulna and at the ankle between the tibial and fibular malleoli. With this technique, two body compartments, fat mass (FM) and fat free mass (FFM), can be determined. Patients with a pacemaker will be excluded from this measurement.

#### Resting energy expenditure

Resting energy expenditure (REE) will be calculated from measurements of oxygen consumption (VO_2_) and carbon dioxide production (VCO_2_) by with a ventilated hood system, in supine position for 30 minutes, with a metabolic monitor (Vmax Encore n29, Viasys Healthcare, Houten, The Netherlands). Before each measurement, gas analyzers will be calibrated with two reference gas mixtures (a. 16% O_2_, 4% CO_2_, bal. N_2 _and b. 26% O_2_, bal. N_2_. (Viasys)). Patients will be monitored during the measurement to prevent movements or sleeping under the hood.

REE will be calculated from oxygen consumption and carbon dioxide production by using the equation of Weir [31].

#### Dietary intake

Dietary intake will be obtained by asking in broad outlines for patients' mean daily intake of food and drinks in the two weeks before admission to the hospital and at three months after discharge.

#### Biochemical parameters CRP, IGF-1, 25(OH)D

Two blood samples per patient will be obtained: the first on the day after inclusion and the second three months after discharge. We will measure CRP, IGF-1 and 25(OH)D in both samples. The blood samples will be centrifuged and stored at -80°C. All blood samples will be analyzed simultaneously after completing full data collection.

C-reactive proteïn (CRP in mg/l) is a member of the class of acute-phase reactants as its levels rise dramatically during inflammation processes. Plasma concentrations of C-Reactive Protein (CRP) will be measured with an automated latex-enhanced immunoturbidimetric assay on a Modular P800 analyzer (Roche Diagnostics, Almere, The Netherlands).

Insuline-like growth factor (IGF-1 in μg/l) will be obtained to observe over or under production of growth-hormone. Serum levels of IGF-1 will be measured with a Immulite 2500 analyzer (Siemens, Deerfield, IL, USA)

Serum 25(OH)D (in nmol/l) will be obtained to observe differences in vitamin D levels after the three month supplementation of vitamin D in the intervention group. This will be determined using a competitive protein binding assay (Nichols Diagnostics, San Juan Capistrano, CA, USA).

All analyses will be performed at department of Clinical Chemistry of the VU University Medical Center.

#### Costs

Costs will be measured from a societal perspective. Direct health care costs include the costs of transmural nutritional support (nutritional supplements plus dietitian), hospitalization, additional visits to other health care providers (general practitioner, medical specialist), prescription and over-the-counter medication, professional home care. Direct non-health care costs of paid and unpaid help and indirect cost of absenteeism of paid and unpaid work will also be included.

Data on the use of nutritional support will be registered by the dietician implementing the transmural nutritional intervention. Data on health care utilization during hospitalization will be retrieved from medical records and the hospital information system. Use of other health care resources after discharge from the hospital will be collected through two identical cost diaries each spanning a period of 6 weeks. Medication data will be obtained from the patients' pharmacies.

Health care utilization will be valued using standard costs from the Dutch guidelines for cost analysis in health care research [32]. If there are no standard costs available, tariffs or prices from health care providers themselves or professional organizations will be used. The costs of medication will be estimated on the basis of prices charged by the Royal Dutch Society for Pharmacy.

#### Economic evaluation

The aim of the economic evaluation will be to determine and compare the total costs for patients receiving either transmural nutritional support or usual care, and to relate these costs to the effects of the interventions.

Incremental cost-effectiveness ratios (ICERs) will be calculated by dividing the difference in mean total costs between the two interventions by the difference in mean effects between the two interventions. The ICERs will be calculated for the primary clinical effect measures of the trial, i.e. functional status and ADL. Cost-utility ratios will also be calculated.

Bootstrapping will be used for pair-wise comparison of the mean differences in total costs between the intervention groups. Confidence intervals will be obtained by bias corrected and accelerated (Bca) bootstrapping using 5000 replications [33]. To estimate the uncertainty surrounding the ICERs bias corrected accelerated bootstrapping (5000 replications) will be used. The bootstrapped cost-effect pairs will be plotted on cost-effectiveness planes and will be used to estimate cost-effectiveness acceptability curves.

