### Procedure

After obtaining patients' informed consent an inventory will be made of nutritional status, nutritional risk profile and possible confounders. This includes the following baseline characteristics:

- sociodemographic data (age, gender, education level, partner status)

- medical history and medical diagnosis

- anthropometry (weight, height, BMI, percentage involuntary weight loss)

- biochemical parameters (CRP, IGF-1, 25(OH)D)

- mental state (MMSE) [18]

- expected care complexity (COMPRI) [19]

Information on disease, disease severity, disease course, treatment and complications will be retrieved from medical records.

Post-discharge practice will be followed and outcome parameters will be collected for all patients at three months after discharge.

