### Statistical analyses

All analyses will be performed according to the intention-to-treat principle. 95% confidence intervals will be calculated for the differences in percentages and means. Logistic regression will be used to analyze dichotomous variables, Poisson regression for the count-variables and linear regression for continuous variables. Ceiling and floor effects will be taken into account in the analysis of the questionnaires.

In order to test the independent contribution of the intervention on the outcome variables, multivariate regression analysis will be used to adjust for the possible confounders.

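### Read literally, the ICERs rest on unadjusted cost and effect differences, which gives up precision that the baseline data already collected could supply

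*Protocol article*

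**What the plan says.** The Economic evaluation section of the Protocol article sets out its estimator in full. The ICER comes from "dividing the difference in mean total costs between the two interventions by the difference in mean effects between the two interventions". For costs, "Bootstrapping will be used for pair-wise comparison of the mean differences in total costs between the intervention groups". For the interval, "Confidence intervals will be obtained by bias corrected and accelerated (Bca) bootstrapping using 5000 replications", and the same number of replications serves the ICERs, the cost-effectiveness planes and the acceptability curves. No covariate appears at any step.

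Three other sections bear on this:

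- **Statistical analyses:** for the outcome variables, "multivariate regression analysis will be used to adjust for the possible confounders".
- **Procedure:** after consent, "an inventory will be made of nutritional status, nutritional risk profile and possible confounders". The list includes age, gender, diagnosis and the COMPRI measure of expected care complexity.
- **Randomisation:** blocks of ten, no stratification mentioned, and allocation revealed once the baseline interview and measurements are finished.

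**The concern.** The Background makes cost-effectiveness the aim of the trial. Patients come from internal medicine, traumatology and vascular surgery wards, and the Discussion calls such patients relatively unselected, so resource use can be expected to vary with case-mix. COMPRI, an instrument meant to anticipate care needs, is recorded before allocation but has no stated place in the analysis of care costs.

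Two things are at stake:

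- **Precision.** If baseline variables predict cost, the unadjusted difference has a larger standard error than the collected data require.
- **Consistency.** If the effect on function is reported after adjustment while the ICER divides by an unadjusted effect, one trial carries two estimates of the same effect, and the cost-effectiveness result rests on the one not given prominence.

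**Working it through.** **Plan's own figures.** The plan gives no figure for costs. Its 80 per group concerns a clinical difference of 20% and has no bearing here. The document states neither a cost SD nor a covariate-cost correlation, so everything below is in units of one cost SD, over an assumed range of R² (the share of cost variance explained by baseline covariates).

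**Inputs.** 100 per arm and 10% loss to follow-up (Feasibility of recruitment and sample size), so 100 × 0.9 = 90 evaluable per arm.

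**Standard errors.** Unadjusted: √(2/n) = 0.149 at n = 90 (0.141 at n = 100). Adjusted: √(2/n) × √(1 − R²). Equivalent gain in patients: 1/(1 − R²).

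| R² assumed | r = √R² | √(1 − R²) | Adjusted SE, n = 90 | SE reduction | Equivalent sample |
|---|---|---|---|---|---|
| 0.01 | 0.10 | 0.995 | 0.148 | 0.5% | × 1.01 |
| 0.10 | 0.32 | 0.949 | 0.141 | 5.1% | × 1.11 |
| 0.20 | 0.45 | 0.894 | 0.133 | 10.6% | × 1.25 |
| 0.30 | 0.55 | 0.837 | 0.125 | 16.3% | × 1.43 |

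The percentage reductions do not depend on n.

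**How far the two estimates may lie apart.** The gap between the unadjusted and adjusted difference has SD √R² × √(2/n). At n = 90 this is 0.015, 0.047 and 0.082 cost SDs for R² = 0.01, 0.10 and 0.30. The unadjusted 95% half-width, 1.96 × 0.149 = 0.292, already includes this component. The same formula applies to the effect in the denominator, with its own R² and SD.

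**Validity and skewness.** Costs were simulated as log-normal (log-SD 1, 100 per arm, 4,000 trials, no true difference), with the covariate correlated with log cost.

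- **Bias and coverage:** at log-scale correlations 0, 0.3 and 0.5, the mean unadjusted difference was within 0.002 SD of zero. Coverage was 95.1%, 95.3% and 95.5%, using a normal-approximation interval and not the planned BCa interval.
- **Precision:** the SD of the estimate fell from 0.1419 to 0.1386 (2.3%) at 0.3 and from 0.1411 to 0.1306 (7.4%) at 0.5. Putting 0.3 and 0.5 straight into the formula gives 4.6% and 13.4%.
- **Why the gain is smaller:** skewness weakens the correlation on the cost scale to r/√(e − 1) = r/1.311, that is 0.229 and 0.381. The formula then gives 2.7% and 7.6%, close to the simulation.

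A second simulation (90 per arm, log-SD 0.75), with R² taken on the cost scale, gave SE ratios of 0.95, 0.92 and 0.86 at R² of about 0.10, 0.19 and 0.26. The formula gives 0.949, 0.900 and 0.860.

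**The case against.** The Economic evaluation section never calls its differences raw or unadjusted. It gives the generic definition of an ICER, and a covariate-adjusted difference is still a difference in means that can be bootstrapped. Costs and Economic evaluation both sit under Outcome parameters, and the Statistical analyses section makes no exception for costs, so adjustment may be intended. A journal article may also leave the covariate list to an analysis plan that is not shown.

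Much of this stands. Unadjusted is the literal reading, not a stated word. A reader might infer that the two sections contradict each other, but the text does not support that, because the Economic evaluation section excludes nothing. The absence of a covariate list is no fault in itself.

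What remains is that the section does not defer its estimator. It specifies the ratio, the bootstrap, the type of interval and the number of replications, and no covariate enters. That is a stated method for which a better one is available from data already planned.

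A reader might also infer that chance imbalance in COMPRI biases the cost-effectiveness answer. It does not: the unadjusted difference is unbiased under randomisation, and its interval already allows for chance imbalance.

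**Conclusion.** The point holds as one of precision and consistency, not validity. Taken literally, the economic evaluation uses unadjusted differences while the trial's outcome analyses are adjusted. The cost to precision ranges from negligible (0.5% of the standard error at r = 0.1) through about 5% at R² = 0.1 to about 16% at R² = 0.3, and is somewhat smaller when a correlation on the log scale is diluted by skewed costs. These figures rest wholly on assumed correlations. No euro amount can be derived, because no cost SD is given.

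Two further inferences are not supported:

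- **Comparison with a cited saving.** The Background quotes €723 per patient from an observational cohort, but also €503 to €11696 from a retrospective cost analysis of nine trials. None is stated as this trial's target.
- **Costs incurred before allocation.** The Costs section says "Data on health care utilization during hospitalization will be retrieved from medical records and the hospital information system" but gives no date from which hospital costs are counted, so it cannot be said that care before randomisation is included.

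**What to change.** Amend the Economic evaluation section as follows:

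1. In each of the 5,000 bootstrap samples, resample patients with cost and effect kept together. Fit a linear regression of total cost, and one of effect, on arm plus the same short prespecified list of pre-randomisation covariates, for example COMPRI, age, sex and admitting ward.
2. Use the two arm coefficients as the cost-effect pair for the cost difference, the ICERs, the planes and the acceptability curves.
3. Report the unadjusted result alongside.

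Restrict the list to variables known before the envelope is opened. The first blood sample is taken the day after inclusion (Biochemical parameters section), and disease course and complications come later, so these do not belong on it.

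The cost is a few sentences and a few lines of code, with no extra data collection. The downside is slightly more analysis work for a gain that may be small if the covariates predict cost weakly.

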For in-hospital patients, studies on cost-effectiveness of nutritional interventions are scarce. In a retrospective cost-analysis of nine randomized controlled trials on nutritional support, the cost savings aggregated between €503 and €11696 per patient in surgical, orthopedic, elderly and stroke patients [6]. A recent observational cohort study showed a cost reduction in patients supplied with ONS of €723 per patient [8]. In a prospective study, a reduction of length of hospital stay with one day was achieved with an investment of €34 per malnourished patient [11].

Cost-effectiveness studies of ONS in the community are lacking and are eagerly awaited for. We do expect that a nutritional intervention in the transmural setting will be accompanied by higher health care costs than usual care, but that these higher costs are negligible compared with the cost-savings they can potentially generate.

The aim of this study is to investigate the cost-effectiveness of transmural nutritional support in malnourished elderly patients after hospital discharge as compared to usual care on changes in activities of daily living. Secondary outcomes include changes in body weight, body composition, quality of life, and muscle strength between intervention and control group.

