### Feasibility of recruitment and sample size

Earlier studies have shown that 30% of the elderly hospital population is malnourished at admission [12-16]. For a clinically relevant difference of 20% in nutritional and functional status with a statistical significance level of 0.05 and a power of 80%, two groups of 80 patients were calculated to be sufficient.

A pilot study showed that inclusion of 140 malnourished patients per year is feasible. Taking into account an expected refusal rate of 30% at inclusion and loss to follow-up of 10% during the three months following discharge, we aim to include two groups of 100, to be reached in approximately two years.

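### BCa bootstrapping is assigned to the ICER itself, a ratio for which BCa limits under-cover when the effect is small and cannot be interpreted when replicates span quadrants

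*Protocol article*

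**What the plan says.** The Economic evaluation section obtains the ICER by "dividing the difference in mean total costs between the two interventions by the difference in mean effects between the two interventions". On the choice of effect it says: "The ICERs will be calculated for the primary clinical effect measures of the trial, i.e. functional status and ADL". Cost-utility ratios are planned as well.

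BCa bootstrapping appears twice in that section. It is first used for confidence intervals for the difference in mean total costs. It is then used for the ratio: "To estimate the uncertainty surrounding the ICERs bias corrected accelerated bootstrapping (5000 replications) will be used". No condition is set on the quadrant of the result or on the effect difference being clear of zero. The section closes with: "The bootstrapped cost-effect pairs will be plotted on cost-effectiveness planes and will be used to estimate cost-effectiveness acceptability curves".

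On the direction of costs, the Background says "We do expect that a nutritional intervention in the transmural setting will be accompanied by higher health care costs than usual care", and continues that "these higher costs are negligible compared with the cost-savings they can potentially generate".

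**The concern.** BCa is a method for interval endpoints. It selects adjusted percentiles from the ordered bootstrap values of a statistic, so it needs a statistic that varies smoothly and whose order means something. The ICER fails on both counts.

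- **Discontinuity.** As the effect difference passes through zero, the ratio jumps between very large negative and very large positive values. If the effect is not clearly different from zero, replicates fall on both sides of the jump.
- **Order.** A cheaper and better result and a dearer and worse result both have negative ratios, so they share one tail of the ordered values. Within the cheaper-and-better quadrant, a more negative ratio is not a better one.

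Cost-effectiveness is the stated aim in the Background. A reader shown BCa limits beside an ICER would take them as a valid 95% interval, and in plausible results they would not be one.

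**Working it through.** **Inputs from the protocol article.** Two groups of 100 with 10% loss to follow-up (Feasibility of recruitment and sample size) leave 100 × 0.9 = 90 evaluable per arm. The bootstrap uses 5000 replications. The article gives no cost mean, cost spread, effect SD or cost-effect correlation, so these are assumed below.

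**The plan's own figure.** The target is given as "For a clinically relevant difference of 20% in nutritional and functional status", with "statistical significance level of 0.05 and a power of 80%, two groups of 80 patients were calculated to be sufficient". Without a base rate or SD, the 80 cannot be reproduced uniquely. For two proportions, 19% against 39% gives 80, but 40% against 60% gives 97. For two means, 80 per group corresponds to d = √(2 × (1.96 + 0.842)² / 80) = √(15.70 / 80) = 0.443 SD. I use this as the benchmark effect.

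**Order (arithmetic only).** Pairs are (cost difference, effect difference), with a positive effect meaning better.

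- (-500, 0.1), (-2,000, 0.4) and the dominated (+1,000, -0.2) all give -5,000.
- (-1,000, 0.1) gives -10,000, while (-1,000, 0.4) gives -2,500. The better result at equal saving has the less negative ratio.

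**Closeness to zero effect.** With 90 per arm the standard error of the effect difference is √(2/90) = 0.149 SD. The chance that the estimate has the wrong sign is Φ(-d/0.149).

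**Coverage.** The BCa limits are the replicate quantiles at Φ(z0 + (z0 + z)/(1 - a(z0 + z))). Here z is the normal quantile for 2.5% or 97.5%, z0 comes from the share of replicates below the estimate, and a from a jackknife. Two sets of simulations used 90 per arm and effect SD 1:

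- Set A: log-normal costs, mean EUR 9,000, SD EUR 6,000, true saving EUR 700; 600 trials, 5000 replicates.
- Set B: log-normal costs, mean 10,000, coefficient of variation 1, cost-effect correlation 0 or -0.3, true saving 1,000 or true extra cost 500; 1000 trials, 2000 replicates. Some saving scenarios were repeated with 1500 trials and 5000 replicates.

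| True effect (SD) | P(wrong sign) | Set A | Set B, saving 1,000 | Set B, extra cost 500 |
|---|---|---|---|---|
| 0.05 | 0.37 | 61.2% | 59.1-61.1% | 67.2-68.1% |
| 0.1 | 0.25 | 70.8% | 73.4-74.7% | 73.3-73.6% |
| 0.2 | 0.09 | 84.3% | 84.2-85.5% | 85.0-86.8% |
| 0.3 | 0.02 | 92.3% | 91.7-92.4% | 92.1-92.4% |
| 0.443 | 0.001 | 95.3% | 93.5-95.1% | 92.7-93.5% |

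With a cost coefficient of variation of 2, a saving of 1,000 and an effect of 0.443 SD, coverage was 91.9%. Monte Carlo error is about √(0.85 × 0.15/1000) = 1.1 points at 85% coverage with 1000 trials.

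The loss is of similar size with a saving and with an extra cost, and it fades as the effect grows. The driver is therefore the small effect, not the saving. At 0.2 SD, 70-75% of trials had more than 2.5% of replicates on each side of zero effect; at 0.443 SD, 14-16% did.

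**Mixing of quadrants.** At 0.2 SD with a saving of 1,000 (correlation 0), replicates averaged 25.6% dearer and better, 57.9% cheaper and better, 4.8% dearer and worse, and 11.6% cheaper and worse. Negative ratios make up 57.9 + 4.8 = 62.7%, of which 4.8/62.7 = 8% come from dominated results.

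**Comparators.** BCa intervals for incremental net benefit (EUR 5,000 per SD) covered 94.0-96.5% in Set A. Percentile intervals for net benefit (0, 5,000 or 20,000 per SD) covered 93.9-95.6% under Set B costs with a saving of 1,000. Plain percentile limits for the ICER covered about 95-99% in Set B. They avoid the under-coverage but not the ordering problem.

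**The case against.** The best defence is that the article never promises confidence limits for the ICER. The phrase about confidence intervals belongs to the cost difference, and the sentence after the ICER sentence turns to planes and acceptability curves. On that reading, the ICER sentence only describes resampling of cost-effect pairs. The article does leave this open. But BCa does not generate replicates; it adjusts interval endpoints. Limits for the ratio are therefore the natural reading, and if only resampling was meant, the sentence names the wrong method.

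It is also true that planes and acceptability curves are planned, are sound, and already show most of what a reader needs. They stand beside the ICER sentence and do not withdraw it. Nor is this a detail left to a fuller document: the method is named here.

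Three stronger readings are tempting, and the documents do not support them.

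- A reader might infer that the trial expects a net saving. The Background expects higher health care costs and describes the offsetting savings only as potential.
- A reader might infer that the limits fail in the most likely results. No passage calls small effects likely, and at the effect that 80 per group could detect, coverage is close to nominal.
- A reader might infer that savings cause the under-coverage. The simulations show a similar loss with an extra cost.

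Finally, the fact that more negative is not better applies to any ICER point estimate among cheaper-and-better results. That is why the quadrant must be reported with it.

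**Conclusion.** The ICER sentence is wrong as written, within a limited scope. The loss of order is arithmetic and needs no assumption. The coverage figures rest on assumed costs, effect SD and correlation. Across the cost scenarios tried, the shortfall from 95% is roughly 20-36 points at 0.05-0.1 SD, 8-11 points at 0.2 SD, about 3 points at 0.3 SD and 0-3 points at 0.443 SD. The limits are thus least reliable when the trial finds little functional effect. When savings occur and the effect is uncertain, dominant and dominated replicates mix and the limits cannot be interpreted, whatever their coverage.

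It would be too strong to say that the economic evaluation as a whole misstates its uncertainty. The BCa interval for the mean cost difference, the planes, the acceptability curves and the clinical analyses do not depend on limits for the ratio.

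**What to change.** Replace the ICER sentence in the Economic evaluation section with:

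> Cost-effect pairs will be bootstrapped (5000 replications). ICERs will be reported as point estimates with their quadrant and the percentage of pairs in each quadrant, without confidence limits for the ratio. Uncertainty will be shown by the planes, the acceptability curves and 95% bootstrap intervals for incremental net benefit over a stated range of willingness-to-pay values.

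Keep BCa for the difference in mean total costs. The same replicates are reused, and no new data are needed. The cost is in presentation: the article gives no accepted value for a unit of the functional measures, so net benefit must be shown over a range and not at a single threshold.
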